#### Secondary outcome measures

Changes in TNSS will be measured by comparing the baseline score with the score at 2 weeks and 1, 3, and 6 months after treatment. VAS and TNNSS will be used to observe supplementary symptoms and severity of symptoms. These will also be evaluated at 2 and 4 weeks and 1, 3, and 6 months after treatment. Peripheral blood IL-4, IL-5, IL-6, IL-8, and IL-10 levels will be measured by Luminex to observe allergic reactions.

All outcome readings will be scored on quantitative scales and summarized as mean values and standard deviation.

#### Recruitment timeline

For an overview of the recruitment timeline, interventions, and all time points of participant evaluation, see Fig. 2.

**Fig. 2 Fig2:**
[figure not shown]
Total trial period and evaluation time points

#### Data collection and management

The research staff will be responsible for the collection of baseline characteristic data and medical results during the screening period. For convenience, all participants’ scores, observation times, AE records, and safety assessments will be consolidated into a single CRF. CRFs must be filled out immediately and accurately after each piece of information is acquired. Participants are required to record in their daily diary any other medications they take during the trial period. Outcome evaluators will examine the outcomes at baseline, 2 weeks (within treatment), 4 weeks (end of treatment), 1 month (within follow-up), 3 months (within follow-up), and 6 months (end of follow-up). Data on nasal and non-nasal symptoms will be collected.

Data monitoring and management will be performed every 3 months by the Clinical Research Center of First People’s Hospital Affiliated to Shanghai Jiaotong University. The clinical research monitor will monitor medical practitioners to ensure all processes are correctly implemented. A data monitoring committee (DMC) has been established independent of the sponsor, and no conflict of interest exists. The DMC is responsible for monitoring trial progression and guaranteeing participant safety. Interim analyses and termination plans for the trial have not been specified, but if the DMC requests interim analyses, these will be supplied. Two assistants will enter all data into an electronic database by double data entry. The statistical manager will be responsible for source data organizing, coding, range checking for data values, and converting data to ensure data quality. The database will be locked after all data have been cleaned. If participants withdraw from the trial, the reasons should be detailed and the rate of withdrawal should be statistically analyzed.

#### Quality control

Before recruitment, the entire research staff involved in the trial including acupuncturists, operational assistants, and research nurses must receive training in advance. Training will include the method for correctly filling out CRFs, blood tests, details of AAP, use of scales, participants’ method of using the medication diary, and follow-up visit skills. Researchers will be examined after training to ensure strict adherence to the trial protocol and consistency of the trial administration process including acupuncture and AAP treatment and evaluation method. The entire research staff will be provided with a written protocol and standard operating procedure documents. All acupuncturists who apply the treatment must have acupuncture licenses from the Ministry of Health of People’s Republic of China and > 5-year clinical experience.

To improve the quality of trial reporting and conduct, we will develop a standard operating procedure manual according to the principles of the CONSORT Extension for Chinese Herbal Medicine Formulas [33] and will thoroughly train all investigators. Intervention details such as acupuncture rationale, needling details, treatment regimen, time selection, practitioner background and confidence, and adequacy of stimulation were extracted and evaluated by CZ and SX according to STRICTA [34].

To ensure data authenticity, a special research team from the Clinical Research Center of Shanghai General Hospital, Shanghai Jiao Tong University School of Medicine, independent of the investigators and sponsors, will externally monitor the trial at the three hospitals every 3 months. An advisory board will follow the trial and provide advice when necessary.

To improve intervention adherence, free treatment and blood tests will be provided to the treatment group for 4 weeks. To ensure that treatment and follow-up run on schedule, participants will be assured of and given monetary compensation at the end of the follow-up period.

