Acupuncture is a component of traditional Chinese medicine (TCM) that was originally believed to work on the principle of the redistribution of qi, the life energy. In TCM, disease is understood to originate from an imbalance or poor flow of qi. Acupuncture has long been used in TCM to treat AR, and studies of this treatment have shown mixed results, with the most rigorous studies showing only modest clinical benefits [21–24]. The 2015 revision of the American Academy of Otolaryngology-Head and Neck Surgery clinical practice guidelines for AR cites a low level of confidence in the evidence to support acupuncture as a treatment option. Acupuncture may be a reasonable option for patients with relatively mild symptoms who wish to minimize medication use and who find its cost acceptable [1]. These results have helped practitioners to improve their use of acupuncture to treat AR. However, high-quality scientific evidence is needed to instruct the clinical application of acupuncture.

Preliminary experiments have found that the use of acupuncture at three nasal acupoints plus acupoint application (AAP) achieve a more persistent effect in the treatment of AR than simple acupuncture alone. Based on this preliminary research, a multicenter, randomized controlled trial (RCT) has been designed in which acupuncture at nonmeridian acupoints and sham AAP will be used with a control group to evaluate the effect of AAP through long-term observation. The purpose of this trial is to answer three questions: (1) Does AAP benefit PAR? (2) How long do the effects last? and (3) Does AAP work by intervening peripheral blood IL-4, IL-5, IL-6, IL-8, and IL-10 levels? Similar research techniques have been applied in previous studies on PAR such as the Total Nasal Symptom Score (TNSS) [25], visual analog scale (VAS) [26], and Total Non-Nasal Symptom Score (TNNSS) [22]. This trial has adopted TNSS, VAS, and TNNSS due to their wide applicability. The trial hypothesis is that AAP will achieve equal or better long-term symptom relief in PAR or severe AR and reduce its recurrence compared to acupuncture alone.

The trial has been registered at acmctr.org AMCTR-ICR-18000179.

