### Randomization

Participants will be randomly assigned at a ratio of 1:1 to a treatment or control group. The randomization sequence was generated using block randomization with a table of randomization. The table contains, in a random order, all possible combinations of a small series of figures, and it assumes an equal probability of a participant being randomly assigned to the treatment or control group. The order of interventions assigned to each block is randomized. The process is repeated for consecutive blocks until all participants are randomized. While receiving the first treatment, participants will be given sequential treatment cards from independent researchers to ensure adequate concealment.

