### Blinding

This will be a single-blind trial. All participants will be treated separately to prevent communication. Except acupuncturists, all relevant parties will be blinded to the intervention groups. Treatments will be administered by two acupuncturists using treatment patches prepared by operational assistants. Due to the nature of AAP, it is difficult to fully ensure blinding among participants allocated to either group. Participants will be required to wait for 120 min in a room, after which their treatment patches will be removed by research nurses. In addition, acupuncturists, operational assistants, and research nurses are instructed to not communicate with participants on any information that might alert them to which group they have been allocated. Participants will be informed that they have an equal chance of allocation to the treatment or control group before research participation. The participants will be blinded to the group they belong to because needle penetration is achieved in all cases. In addition, outcome evaluators and statistical analysts will be blinded to the groupings and will not be involved in any part of the treatments during trial to ensure no statistical bias in the results.

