#### Efficacy analysis

Efficacy data analyses will be conducted on an intention-to-treat population. All participants initially included in any group will be considered in statistical analysis. Analysis of efficacy will be performed per-protocol and will include all participants who complete the entire research. Descriptive statistics will be used to compare serum indicators between the two groups. Regarding the primary and secondary outcome measures, a two-sample *t* test or Wilcoxon rank-sum test will be used to compare differences between both groups from baseline to the end of treatment (*p* < 0.05 will be considered statistically significant). The mean and standard deviation values of these parameters will be reported. Regarding repeated measures data, repeated measures analysis of variance will be performed after meeting spherical symmetry requirements. SPSS 16.0 will be used for all statistical calculations.

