#### Missing data analysis

All data used in the main statistical analysis should be collected by the fourth week of the treatment and by the 6-month follow-up. To avoid missing data, participants who complete the trial and provide completed data will be financially compensated. The investigators have a wealth of experience from previous trials in managing participants and collecting data. Participant contact information will be recorded and researchers will keep in touch with them through various means of communication during the treatment and follow-up periods.

If data are not obtained, the time and reason for missing data will be recorded and the assumed missing data mechanism will be analyzed. For these missing data, a multiple imputation adjustment approach will be used. After the main analysis, sensitivity analysis will be performed for the various datasets to enable the assessment of the impact of missing data on the results.

A detailed statistical analysis plan will be written by an independent statistician.

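### Free treatment and blood tests are promised to the treatment group by name and to no one else, which sits badly with participant blinding, even-handed retention and a two-arm cytokine comparison

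*Protocol article*

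**What the plan says.** All references are to the protocol article.

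- **Quality control:** with the stated aim of better adherence, "free treatment and blood tests will be provided to the treatment group for 4 weeks". The next sentence offers a different incentive without limiting it to an arm: "participants will be assured of and given monetary compensation at the end of the follow-up period".
- **Missing data analysis** repeats the general incentive, tied to completion: "participants who complete the trial and provide completed data will be financially compensated".
- **Randomization** fixes the vocabulary: "Participants will be randomly assigned at a ratio of 1:1 to a treatment or control group". The Intervention section then uses the two names as separate subheadings.
- **Blinding:** "The participants will be blinded to the group they belong to because needle penetration is achieved in all cases". Staff are also told to say nothing that could alert a participant to the assigned group. The same section concedes that participant blinding is hard to guarantee.
- **Cytokines:** the Background asks "Does AAP work by intervening peripheral blood IL-4, IL-5, IL-6, IL-8, and IL-10 levels" as the third trial question. Secondary outcome measures lists the five interleukins with no restriction by arm. Efficacy analysis says "Descriptive statistics will be used to compare serum indicators between the two groups".

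**The concern.** A benefit given to one arm of a participant-blinded trial is a cue to allocation. Here the primary outcome is change in the Total Nasal Symptom Score (TNSS), and the visual analog scale and non-nasal scores are secondary. All three depend on what participants report, so belief about allocation can move them.

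The benefit is also introduced expressly to improve adherence. If it works and is confined to one arm, adherence and retention will differ by arm by design. That matters because the Follow-up section removes participants who discontinue or deviate, together with their latest outcome data, and Efficacy analysis includes an analysis of those who complete.

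Finally, a between-group cytokine comparison needs control blood as much as treatment-arm blood, yet the only sentence on providing blood tests names the treatment group.

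**Working it through.** The article states no figure on this point, so the main check sets the passages side by side.

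1. **Does the term mean one arm?** Yes. Randomization and the Intervention subheadings use treatment group and control group as the names of the two arms.
2. **Could it be shorthand for everyone enrolled?** Quality control itself uses the general word, participants, in the next sentence for the monetary compensation. As written, the text separates a benefit for one arm from a benefit for all.
3. **Is the same offer made to controls elsewhere?** No such statement appears in the article.
4. **Does it fit the blinding text?** Not as written. Being charged, or seeing that free tests are absent, is the kind of information that staff are told not to convey.
5. **Does it fit the cytokine text?** Not as written. Secondary outcome measures and Efficacy analysis presuppose blood from both arms.
6. **Would unequal retention reach the results?** Yes, through the exclusion rule under Follow-up and the completer analysis. The intention-to-treat analysis with multiple imputation limits this. It does not reliably remove it if dropout depends on unobserved symptoms or on perceived allocation.

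**Side check: is the harm a loss of power?**

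Inputs from Sample size calculation: 49 per group needed, 60 per group recruited, 20% dropout, alpha 0.05, power 80%. Two-sided alpha is an assumption, because the sidedness is not stated.

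The plan's own inflation: 49 × 1.2 = 58.8, so 59; 49 / (1 − 0.2) = 61.25, so 62. The stated 60 is close to both. At 20% dropout, 60 × 0.8 = 48 per arm remain.

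Standardised effect at which 49 per arm gives 80% power: d = √(2/49) × (1.960 + 0.842) = 0.566. It is back-calculated from 49, because 49 itself is not reproduced from the means, SDs and delta stated in that section.

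Power = Φ( d / √(1/n_T + 1/n_C) − 1.960 ), with n = 60 × (1 − dropout). All splits below other than 20/20 are assumptions.

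| Dropout, treatment / control | n_T / n_C | Power |
|---|---|---|
| 20% / 20% | 48 / 48 | 0.792 |
| 15% / 25% | 51 / 45 | 0.790 |
| 10% / 30% | 54 / 42 | 0.786 |
| 5% / 35% | 57 / 39 | 0.777 |
| 10% / 40% | 54 / 36 | 0.749 |
| 20% / 40% | 48 / 36 | 0.728 |

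The first four rows average 20% dropout. Across them power falls by at most 0.792 − 0.777 = 0.015. The last two rows also raise the average, to 25% and 30%, so their larger losses are not due to imbalance alone. Imbalance costs little power; what remains is bias.

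**The case against.** The strongest reply is that the sentence is loosely worded and means the 4-week treatment period for everyone. The article never says that controls pay or that their blood is not taken. It describes both treatments as 12 sessions over 4 weeks, and it lists the cytokines without restriction by arm. This stands as a possible reading and limits how firmly the point can be put. It does not remove the need for a correction, because staff could follow the sentence as written.

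A second reply is that a control would have to be charged, or learn that the other arm is not, before anything was revealed. Participants are treated separately and staff are told not to disclose. That also stands: this is a conflict in the text, not a demonstrated breach of blinding.

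Third, there is an incentive common to both arms, withdrawal rates will be analysed, and sensitivity analyses for missing data are planned. These soften the retention concern. They do not make the additional benefit equal between arms.

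A reader might also infer that the cytokine question has only a descriptive comparison, or that no blood schedule exists. The documents do not support either inference. Efficacy analysis goes on to apply a two-sample *t* or rank-sum test to the secondary outcomes, which include the cytokines. Table 1 has no blood row, but Fig. 2, which gives the evaluation time points, is not shown. The form of the cytokine model can be left to the statistical analysis plan.

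**Conclusion.** The point holds in a limited form. As written, Quality control gives one named arm a visible benefit meant to improve adherence, and this conflicts with the Blinding section and with a cytokine comparison across both groups. That no control receives it is inferred from silence.

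A reader might conclude that the offer does reveal allocation and does drive unequal dropout. The article supports only that it could, if the sentence is implemented literally.

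The size of the bias cannot be derived from the document. Any figure would rest on an assumed share of controls who guess their group and an assumed shift in their scores. The delta of 0.2 under Sample size calculation is no yardstick either, since its unit and role are not defined. The direction is not fixed: controls who guess their allocation would tend to report worse scores, which favours AAP, whereas selective loss of poorly relieved controls would work the other way in a completer analysis. The loss of power from imbalance alone is small, about 1.5 percentage points or less in the cases tried. The change should be made, because it is simple and removes an avoidable source of bias from a symptom-score primary outcome.

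**What to change.** Replace the sentence under Quality control with: *treatment sessions and blood tests will be provided free of charge, on the same terms and schedule, to participants in both groups.* Reconcile it with Blinding, Secondary outcome measures and Efficacy analysis. Since Trial status reports that recruitment has begun, also check what controls are currently told and charged, and record the answer.

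If both arms already receive these free, the cost is one clarifying sentence. If not, the sponsor bears up to 60 × 12 = 720 control sessions plus the controls' blood tests, whose number per participant the article does not state. A protocol change would also go to the three ethics committees, which have received all protocol versions.

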### Statistical analysis

#### Sample size calculation

The trial will test two groups in parallel. Sample size calculation was performed using SAS 9.3 (SAS Institute Inc., Cary, NC, USA) at the Clinical Evaluation Center of First People’s Hospital Affiliated to Shanghai Jiaotong University. The mean change in TNSS before and after treatment was used as the indicator of efficacy evaluation in sample size calculation. Other research has shown a mean TNSS change of 2.53 ± 4.74 after acupuncture treatment [22] and 2.75 ± 1.06 after AAP [35]. Based on these findings, the appropriate trial sample size with power of 80%, alpha value of 0.05, and acceptable delta value of 0.2 was calculated. The results show that a clinically important difference can be detected by a sample size with at least 49 in each group. Accordingly, this number was increased to 60 per group (a total of 120) to allow for a predicted 20% dropout rate.

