## Methods/design

### Design

The study is designed as a multicenter, parallel-group, randomized, and single-blind trial to compare AAP with a sham acupuncture for PAR treatment. The trial was designed according to the Standard Protocol Items: Recommendations for Interventional Trials (SPIRIT) statement (Fig. 2) [27], and conforms to the Consolidated Standards of Reporting Trials (CONSORT 2010) guidelines (Fig. 1) and Standards for Reporting Interventions in Controlled Trials of Acupuncture (STRICTA) [28, 29].

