#### Control group

The control group will receive shallow needling at sham Yintang (EX-HN3), sham Yingxiang (LI20), sham Shangyingxiang (EX-HN8), sham Feishu (BL13), sham Dazhu (BL11), and sham Taiyuan (LU9). Each of these acupoints is a nonacupoint located at a different physical location to the actual acupoints. The placebo ointment is composed of buckwheat powder and coke, resulting in an ointment appearing similar to the AAP ointment.

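### The sample size rests on TNSS changes after acupuncture and after AAP, but the control arm is sham; no sham input supports the stated 80% power

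*Protocol article*

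**What the plan says.** Under Sample size calculation, the indicator is the mean TNSS change, and two published figures are given: "Other research has shown a mean TNSS change of 2.53 ± 4.74 after acupuncture treatment [22] and 2.75 ± 1.06 after AAP [35". The calculation is said to follow from them, with "power of 80%, alpha value of 0.05, and acceptable delta value of 0.2". The conclusion is that "a clinically important difference can be detected by a sample size with at least 49 in each group", raised to 60 per group for 20% dropout.

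The arms are described elsewhere. The Design section calls this a "randomized, and single-blind trial to compare AAP with a sham acupuncture for PAR treatment". The Control group section says "The control group will receive shallow needling at sham Yintang (EX-HN3), sham Yingxiang (LI20), sham Shangyingxiang (EX-HN8" and so on. It describes every control site as a non-acupoint and gives the placebo ointment as buckwheat powder and coke. The Efficacy analysis section compares these two groups with a two-sample t test or a Wilcoxon rank-sum test. No arm receives real acupuncture without the ointment.

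**The concern.** A power statement needs an assumed outcome in each randomised arm, or at least an assumed difference and SD between them. Here the only figure that is not for AAP is labelled as a response to acupuncture, a treatment that neither arm receives on its own. The hypothesis in the Background also names acupuncture alone as the comparator, so the sizing inputs match that sentence but not the randomised arms. The pilot described in the Discussion cannot fill the gap, because its arms were AAP, acupuncture only and loratadine.

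At stake is how the primary result is read. The report would carry a claim of 80% power for a clinically important difference, while the effect over sham that the trial was meant to detect is stated nowhere. A non-significant week-4 result could then be taken as evidence against an effect of a size the trial may never have been able to detect.

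**Working it through.** **Inputs from Sample size calculation.** Acupuncture 2.53 (SD 4.74); AAP 2.75 (SD 1.06); power 80%; alpha 0.05, taken as two-sided because the section does not say; delta 0.2, with unit and role not given; 49 per group before dropout. Allocation is 1:1 (Randomization). There is no sham mean or SD.

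**Step 1: can 49 be reproduced?** For two means, n per group = (1.960 + 0.842)² × (s₁² + s₂²) / d², where the first factor is 7.849.

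- d = 2.75 − 2.53 = 0.22 with SDs 4.74 and 1.06: 7.849 × (22.468 + 1.124) / 0.0484 = 3,826.
- d = 0.22 with SD 1.06 in both arms: 7.849 × 2.247 / 0.0484 = 365.
- Delta as a raw difference of 0.2: 441 (SD 1.06 in both) or 4,630 (SDs 4.74 and 1.06).
- Delta as a standardised effect of 0.2: 393.
- Delta as a non-inferiority margin, true difference 0.22, SD 1.06: 100 at one-sided 0.025, or 79 at one-sided 0.05.

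None gives 49. Two near misses do not fit the stated design. A one-sample formula with effect 0.42 and SD 1.06 gives 50, but leaves out the factor 2 needed for two groups. A difference of 2.75 with SD 4.74 gives 47, but requires a sham change of zero, which the protocol does not state. The dropout step is close enough: 49/0.8 rounds up to 62, 49 × 1.2 is 59, and the plan has 60.

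**Step 2: power of 49 per group for the gap between the cited means.** For a Welch t test with SDs 4.74 and 1.06, SE = √((4.74² + 1.06²)/49) = √(23.591/49) = 0.694, with about 52.8 degrees of freedom. The noncentrality is 0.22/0.694 = 0.317, and power is 0.061, or about 6%. With SD 4.74 in both arms it is also about 6%. With SD 1.06 in both arms it is about 18% (normal approximation).

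**Step 3: what 49 per group can detect.** The difference needed for 80% power at two-sided 0.05, from the noncentral t:

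| SDs (control, AAP) | SE | Difference needed |
|---|---|---|
| 1.06, 1.06 | 0.214 | 0.61 |
| 4.74, 1.06 | 0.694 | 1.98 |
| 4.74, 4.74 | 0.958 | 2.71 |

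**Step 4: dependence on the missing sham mean.** The sham changes below are assumptions, chosen only to show the range; the AAP change is held at 2.75. The first SD column uses the normal approximation, the others the noncentral t.

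| Assumed sham change | Power, SD 1.06 in both | Power, SDs 4.74 and 1.06 | Power, SD 4.74 in both |
|---|---|---|---|
| 2.0 | 94% | 19% | 12% |
| 1.5 | >99% | 42% | 25% |
| 1.0 | >99% | 70% | 44% |
| 0.5 | >99% | 89% | 64% |
| 0 | >99% | 97% | 81% |

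Over this range, power against sham runs from 12% to more than 99%. The protocol gives no basis for choosing a row or a column.

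**The case against.** The section never says that 2.53 ± 4.74 was the control-arm input. It lists two findings and says the calculation was based on them; the SAS set-up and the two sources are not visible. That is fair: the role is inferred from there being two groups and two values, one of them labelled AAP. But if the acupuncture figure was only background, no control-arm assumption is stated at all, and the correction is the same.

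A reader might go further in three ways, and the document supports none of them.

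- **That the 80% is valid power for AAP versus acupuncture.** It is not; step 2 gives about 6% with the two cited SDs.
- **That the trial was planned on a difference of 0.22.** That figure is only the gap between the two cited means. The protocol's own delta is 0.2, and neither value leads to 49.
- **That the trial is underpowered against sham.** If sham patients improve less than acupuncture patients, the true difference exceeds 0.22 and the size could be ample. Every assumed sham change in step 4 lies below 2.53, and in each SD column power is higher than it is for 0.22.

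It is also right that the cited SDs come from the very inputs being questioned. Steps 3 and 4 therefore show all three SD patterns, including the favourable one, and none can stand as the sham SD. Nor does the gap make the result unreadable: the observed difference and its confidence interval can still be interpreted. What is lost is a planned effect to set them against.

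**Conclusion.** The concern holds in a limited form. The comparator in the sizing inputs is not the comparator randomised, no sham-arm assumption is stated, and the claim of 80% power for a clinically important difference is unsupported for AAP versus sham. The same inputs do not support it for AAP versus acupuncture. True power against sham is unknown rather than shown to be low. With 49 evaluable per group, 80% power needs a true difference of about 0.6 to 2.7 points across the SD patterns the cited figures allow. This assumes two-sided alpha 0.05, a two-sample t test on TNSS change, and SDs of 1.06 or 4.74 in each arm. The cited sources were not available, so their figures are taken as the protocol labels them.

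**What to change.** In Sample size calculation:

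1. Replace the acupuncture figure with an expected TNSS change and SD for sham needling plus placebo ointment, and give the source.
2. State the assumed AAP-minus-sham difference at week 4, whether alpha is one- or two-sided, and what delta 0.2 means.
3. Withdraw the present statement of 80% power, and recompute the size from the new inputs.
4. Say what the planned size delivers: with about 49 evaluable per group and two-sided alpha 0.05, 80% power for about 0.6 points (SD 1.06 in both arms), 2.0 points (SDs 4.74 and 1.06) or 2.7 points (SD 4.74 in both arms). Mark these SDs as provisional until a sham SD is given.

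The hypothesis sentence in the Background should name the same comparator as the randomised arms.

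The direct cost is a rewritten section and a search for a sham estimate. The downside is a less favourable stated detectable difference. Whether 60 per group remains adequate cannot be promised in advance; it depends on the sham figures, and recruitment has already begun.

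### The stated inputs do not give 49 per group at 80% power: a two-sided comparison built on them has about 6% power, and 60 per group leaves 48, not 49, after 20% dropout

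*Protocol article*

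**What the plan says.** All of this is in the protocol article, Sample size calculation. The calculation is based on the mean change in TNSS, which is also the primary outcome. Its inputs come from two published studies: a "mean TNSS change of 2.53 ± 4.74 after acupuncture treatment" and a change of "2.75 ± 1.06 after AAP". Power is set at 80%, with an "alpha value of 0.05" and a delta described only as "acceptable delta value of 0.2 was calculated". The section does not say whether delta is a difference in points, a standardised effect or a margin, nor whether the test is one- or two-sided.

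The result is given as "The results show that a clinically important difference can be detected by a sample size with at least 49 in each group". For attrition, "this number was increased to 60 per group (a total of 120) to allow for a predicted 20% dropout rate".

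Efficacy analysis plans a between-group two-sample t test or Wilcoxon rank-sum test at p < 0.05. Randomization gives the allocation ratio as 1:1.

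**The concern.** Both means, both SDs, alpha, power, delta and the resulting n are on the page, so the result can be recomputed. The difference between the means is 0.22 points and one of the SDs is 4.74. Forty-nine per group is far too few for a contrast that small against that much variability.

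The paragraph is the trial's only statement of what it can detect. It says that a clinically important difference is detectable, yet the only effect sizes it shows are 0.2 and 0.22. A reader who accepts it could take a non-significant primary result as adequately powered evidence of no effect. The hypothesis in the Background, that AAP gives equal or better relief, makes it easier still to read non-significance as equality.

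**Working it through.** **Inputs (Sample size calculation).** Means 2.53 and 2.75; SDs 4.74 and 1.06; alpha 0.05; power 80%; delta 0.2; dropout 20%. Two-sided testing is assumed first, because it fits the planned between-group test at p < 0.05.

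**Attempt to reproduce 49.** For two equal groups,

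n per group = (1.960 + 0.8416)² × (SD₁² + SD₂²) / d².

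- (1.960 + 0.8416)² = 7.849
- 4.74² + 1.06² = 22.468 + 1.124 = 23.591, so the root-mean-square SD is √(23.591/2) = 3.43
- d = 2.75 − 2.53 = 0.22: 7.849 × 23.591 / 0.0484 = 3,825.7, so 3,826 per group
- d = 0.20: 7.849 × 23.591 / 0.04 = 4,629.1, so 4,630 per group

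These are about 78 and 94 times the stated 49. The figure is not reproduced.

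**Power of the stated design** (noncentral t, two-sided 0.05, SD 3.43):

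| n per group | d = 0.20 | d = 0.22 |
|---|---|---|
| 49 | 5.9% | 6.1% |
| 60 (no dropout) | 6.1% | 6.4% |

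**Other readings**, tried because sidedness and the role of delta are not stated:

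| Reading | n per group for 80% | Power at 49 |
|---|---|---|
| Superiority, one-sided 5%, SD 3.43, d = 0.22 | 3,014 | about 9% |
| Superiority, two-sided, SD 1.06 in both arms, d = 0.22 / 0.20 | 365 / 441 | 17% / 15% |
| 0.2 as a standardised effect, two-sided | 393 | about 17% |
| Non-inferiority, margin 0.2, true benefit 0.22, SD 3.43, one-sided 2.5% / 5% | 1,050 / 827 | about 9% / 15% |
| As above, SD 1.06 in both arms, one-sided 2.5% / 5% | 100 / 79 | about 49% / 62% |

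In the non-inferiority rows the effective distance is 0.22 + 0.20 = 0.42. If the true difference is zero, the requirement is larger: at least 348 per group, even with SD 1.06 and one-sided 5%.

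**Difference the design can detect** (two-sided 0.05, 80% power, noncentral t):

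- 49 per group: standardised effect 0.572, which is 1.96 points at SD 3.43 or 0.61 at SD 1.06
- 48 per group: 1.98 points at SD 3.43 or 0.61 at SD 1.06

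**Dropout.**

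- 60 × (1 − 0.20) = 48, one short of 49
- 49 / (1 − 0.20) = 61.25, so 62 per group (124 in total)
- 1 − 49/60 = 18.3%, the largest loss that still leaves 49
- 49 × 1.20 = 58.8, which suggests that n was multiplied by 1.2 instead of divided by 0.8 and then rounded up to 60

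**The case against.** Three objections deserve an answer.

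First, 49 can be reached from numbers in the paragraph. Taking 2.53 as the between-group difference with SD 4.74 and a margin of 0.2 (distance 2.73) gives 49 per group with a t-based formula at one-sided 2.5%. Taking 2.75 with SD 4.74 gives 46.6, and dividing by the Wilcoxon efficiency of 0.955 gives 48.8, so 49. These may explain where the figure came from. They do not support it, because each treats a within-group change as the difference between groups and ignores the other arm's mean and SD.

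Second, 0.22 contrasts two active treatments taken from separate studies, while the control here is shallow needling at nonacupoints with placebo ointment. The true AAP-versus-sham difference could be larger, and the document does not give it. This stands: 6% is the power for the inputs the protocol chose, not a forecast for the trial. It does not rescue the paragraph, which bases its n on those inputs.

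Third, sidedness, the meaning of delta and the actual SAS inputs may be in the full protocol or the planned SAP. Delta 0.2 also equals 1 − 0.80, so it could be a slip for beta. Either is possible, but the published paragraph says its result follows from the inputs shown, and it does not. If delta was meant as beta, the remaining difference is 0.22, which still needs 3,826 per group.

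The dropout error is one participant per group, and the finding does not depend on it.

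**Conclusion.** The concern holds. No two-group comparison that uses both stated means and both stated SDs gives 49 per group, and the requirement on the most direct reading is about 78 to 94 times larger. Power at 49 per group is about 6% for a two-sided superiority test. It is about 9% to 15% on the other readings tried that keep both SDs. It is at most about 62% on the most favourable one, non-inferiority at one-sided 5% with the larger SD discarded.

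The 6% assumes a two-sided test at 0.05, a true difference of 0.20 to 0.22 points and the SDs as quoted. The conclusion that 80% is not reached does not depend on sidedness or on which role delta plays.

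This does not show that 120 participants are too few. With 48 evaluable per group the trial has 80% power for about 2.0 points if the SD is 3.43, or about 0.6 if it is 1.06. Whether such a difference matters clinically is not addressed in the protocol. The dropout statement is also wrong, by a small amount.

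**What to change.** Keep 120 participants and rewrite the paragraph around what that number delivers. For example: with 60 randomised and 48 evaluable per group (20% dropout), two-sided alpha 0.05 and an SD of 3.43 for the change in TNSS, the trial has 80% power to detect a between-group difference of about 2.0 points; if the SD is 1.06, about 0.6 points.

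Also:

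- Withdraw the statement that 49 per group suffices for the quoted inputs and a delta of 0.2.
- State whether delta is a raw difference, a non-inferiority margin or a standardised effect, and whether the test is one- or two-sided. If it was a slip for beta, say so.
- Say why the chosen SD is suitable for a sham-controlled comparison, since the two sources differ more than fourfold (4.74 / 1.06 = 4.5), and whether the detectable difference is regarded as clinically important.
- Correct the dropout sentence: 60 per group leaves 48 after 20% loss, and leaves 49 only if loss is at most 18.3%.
- If the SAS calculation used other inputs, publish those with the resulting n.

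The cost is wording in the protocol and SAP, with no additional participants. The detectable difference the sponsor can claim becomes less favourable than the paragraph now implies.
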